## Participants who meet the study's inclusion criteria will be invited to attend the clinical outpatient clinic at UNINOVE, São Paulo, Brazil, to receive dermatological treatment from the dermatologist (principal investigator) between March 2024 and October 2024 (end of treatments). The final one-year follow-up will occur in October 2025. Those who agree to participate will sign the Informed Consent Form (ICF) after a detailed verbal and written explanation provided by the principal investigator.

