**3.2. Calibration and Training of Evaluators**

After approval by the Research Ethics Committee, the calibration phase will begin. Participants included in the research will be invited to participate in this specific part of the study. After receiving verbal and written explanations, those who agree to participate will sign a specific Informed Consent Form for calibration. The principal investigator (dermatologist) will collect all the study outcomes, and therefore, only this investigator will undergo calibration. He will evaluate 5 participants with actinic keratosis lesions on the face. Each of these 5 participants will be evaluated (T0), and the lesions will be quantified. The 5 participants will be seen in sequence and reassessed after 1 hour. The same evaluation (lesion recount) will be performed (T1), and the results will be recorded. The Intraclass Correlation Coefficient (ICC) will be calculated to assess the intra-examiner agreement between T0 and T1 values. A value of ≥ 0.80 will be considered adequate regarding the agreement on the number of lesions. These procedures are important to maximize the reproducibility of the evaluations. These participants will receive dermatological treatment for actinic keratoses as needed. These assessments will not be part of the study but will confirm the intra-examiner agreement.

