**3.5. Randomization**

To randomly assign participants to the experimental groups, a random draw of 144 numbers will be conducted using the website <https://www.sealedenvelope.com/>. The group distribution will be identical (1:1:1:1) for the four groups. The distribution will be carried out in blocks (24 blocks of 6 participants). Opaque envelopes will be labeled with sequential numbers, and inside each envelope will be information regarding the corresponding experimental group, according to the order obtained in the draw. The envelopes will be sealed and will remain unopened in numerical order until the time of lesion treatment. The draw and preparation of the envelopes will be performed by an individual not involved in the study. Immediately before the treatment of the lesions, the investigator responsible for the treatment will open the envelope (without altering the numerical sequence) and will proceed with the indicated procedure.

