**3.6. Blinding of the Study**

Only the investigator responsible for performing the treatments (who will open the randomization envelopes) will know which treatment is assigned to each participant. This investigator will reveal the identification of each group to all involved in the study after the statistical analysis of the data.
Therefore, the investigator responsible for data collection and their assistant will be blinded to the treatments assigned to the groups. The participant and the statistician will also be blinded to the type of treatment received.

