**3.10. Study Outcomes**

The primary outcome variable of the study will be:

**• Complete remission** - Quantitative assessment: a count of lesions with a complete response will be performed, meaning those that show total disappearance after treatment. These lesions will be clinically evaluated at 30 days, 3, 6, and 12 months post-treatment, and the number of lesions at these time points will be compared to the baseline. Both absolute and relative lesion counts will be considered. To avoid variability in counting, only one researcher will conduct the counts. This researcher will be calibrated before the study begins. Complete lesion remission will be defined as 100% remission of lesions after 12 months of treatment, as Jansen et al. (2019) described.

The secondary outcome variables will be:

• **Treatment success** - Evaluation of the proportion of participants who show at least a 75% reduction in the initial number of actinic keratosis lesions in the treatment area after the last day. Assessments will be conducted at 30 days, 3, 6, and 12 months. Both absolute and relative lesion counts will be considered. Treatment success will be defined as complete remission in at least 75% of participants over 12 months, as Jansen et al. (2019) established.

**• Recurrence rate** - The recurrence rate of actinic keratoses will be defined as the reappearance of lesions in previously treated areas. Recurrence will be evaluated at the same follow-up periods, namely 30 days, 3, 6, and 12 months after treatment completion. Recurring lesions will be quantified, considering both absolute and relative numbers of lesions. These lesions will be monitored and re-treated at the end of the study unless malignancy is present, in which case they will be treated immediately.

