At the end of the treatment, if lesion worsening is observed in any of the groups not treated with the gold standard (G1), which is unlikely given previous studies with lower concentrations and satisfactory results, or if the treated lesions recur in any group, a local procedure may be performed at no cost to the participant. This outpatient procedure, known as cryotherapy, is non-invasive but more destructive than the proposed treatment in this protocol. It involves the application of liquid nitrogen with the Cryac® device to freeze the lesion, resulting in its local destruction. The procedure may cause blistering and a mild, transient burning sensation and may leave some scarring. It will be performed in a specialty outpatient clinic or private clinic, with follow-up care as needed (BAKER, 2017).

• **Prevention of Squamous Cell Carcinoma (SCC)** - If lesion malignancy occurs during the follow-up period, the gold standard treatment, surgical intervention, will be applied. Participants will be continuously monitored to prevent the development of SCC in the treatment area throughout the study. Participants will remain in the study since follow-ups consist only of monitoring. Malignant lesions will be quantified, considering both absolute and relative numbers. The principal investigator will perform dermatoscopy at no cost to the participant, and if malignancy is suspected, the lesion will be excised in a procedure known as "minor surgery." This is a routine dermatological procedure performed on an outpatient basis, without sedation or hospitalization, using local anesthesia. The patient will be discharged on the same day. The surgery involves removing a small amount of skin tissue containing the lesion, suturing the skin to close the wound, and applying a dressing. Sutures should be removed within 7 to 10 days after surgery. The tissue removed during the minor surgery will be The specimen is placed in a formalin container provided by the laboratory and sent to a pathology laboratory for diagnostic confirmation. The procedure can be performed at a specialty outpatient clinic or private clinic. As expected with minor surgery, scarring and temporary pigmentation changes may occur, which will improve over time.

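### Cryotherapy for worsening lesions is offered only outside the control arm, so using the rule can reveal allocation, and its stated time does not match the rule for recurring lesions

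*Protocol*

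**What the plan says.** Section 3.10 (Study Outcomes) gives cryotherapy two triggers in one sentence. The first covers worsening and leaves out the control arm: "if lesion worsening is observed in any of the groups not treated with the gold standard (G1"). The second covers recurrence and leaves out no one: "or if the treated lesions recur in any group, a local procedure may be performed at no cost to the participant". The sentence times the procedure to the end of treatment. Just before it, the recurrence-rate outcome sets a different time for recurring lesions: "These lesions will be monitored and re-treated at the end of the study unless malignancy is present".

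On who observes what, section 3.2 states: "The principal investigator (dermatologist) will collect all the study outcomes". Section 3.6 (Blinding) adds that "the investigator responsible for data collection and their assistant will be blinded to the treatments assigned to the groups". The same section makes the investigator who gives the treatments the only person who knows the allocation, and says when others learn it: "This investigator will reveal the identification of each group to all involved in the study after the statistical analysis of the data".

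Section 3 (Material and Methods) dates treatment and follow-up separately: "between March 2024 and October 2024 (end of treatments). The final one-year follow-up will occur in October 2025". Table 1 in section 3.9.1.1 gives the number of sessions as one.

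**The concern.** A care rule that depends on the arm does not fit a trial in which the assessor and the participant are meant not to know the arm. Two things are at stake whatever the timing. A participant in G1 whose lesions worsen without recurring and without suspected malignancy is not offered the free procedure that a participant in G2, G3 or G4 is offered. And whether the procedure is offered carries information about allocation before the code is due to be released.

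A third matter depends on timing. If lesions can be frozen during follow-up, some would be destroyed before the 12-month count that defines complete remission, and for worsening this could happen in the three experimental arms only. The protocol also warns that cryotherapy can scar, so the 12-month ratings of skin texture and pigmentation could be touched as well.

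**Working it through.** The plan states no figure on this point, so the check compares the text and adds one short calculation.

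**1. Does the trigger depend on the arm?** Worsening: G2, G3 and G4. Recurrence: all four groups. Both stand in one sentence, so the omission of G1 from the first is explicit.

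**2. Who could apply it?** The principal investigator collects every outcome (3.2), and the data collector is blinded (3.6). The person who sees worsening therefore cannot tell whether the rule applies. The treating investigator knows the allocation and could.

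**3. What does the offer reveal?** Section 3.5 states: "The group distribution will be identical (1:1:1:1) for the four groups". The prior chance of G1 is therefore 1/4 = 25%.
- Cryotherapy given for worsening: the chance of G1 becomes 0%, if the rule is followed.
- A worsened lesion left unfrozen: let q be the fraction of eligible worsened cases that are frozen in G2 to G4, and assume that worsening is equally common in all arms. Then P(G1) = 0.25 / [0.25 + 0.75 × (1 − q)].
  - q = 0: 0.25/1.00 = 25%
  - q = 0.5: 0.25/0.625 = 40%
  - q = 0.8: 0.25/0.40 = 62.5%
  - q = 1: 0.25/0.25 = 100%

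The protocol gives no q, so these values show a range and are not a forecast.

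**4. Is the code still closed when the rule is used?** A participant treated in March 2024 reaches month 12 in March 2025, 7 months before the final follow-up in October 2025 and before any analysis. If the end of the study means October 2025 for everyone, that is still before the analysis after which groups are to be revealed. On either reading the assessor is still meant to be blinded.

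**5. Do the two stated times agree?**
- For two different times: there is one session, section 3 places the end of treatments a year before the final follow-up, and the recurrence outcome counts its visits from completion of treatment.
- For one time, the end of study: the primary outcome refers to 12 months of treatment, which can only mean 12 months of follow-up. The SCC paragraph says that follow-up visits are for monitoring only.

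If the end of treatment is read as the calendar date in section 3, October 2024, a participant treated in March 2024 is then 7 months into follow-up. The 30-day, 3-month and 6-month visits are past and the 12-month count is 5 months away. An early reading is therefore possible in practice, although it is the less likely intent.

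**6. Consequence for complete remission.** Cryotherapy after the participant's 12-month count: no effect. Cryotherapy before it: lesions are removed ahead of the count, for worsening in three arms and for recurrence in all four. The documents give no worsening rate and no cryotherapy uptake, so the size of any bias cannot be calculated.

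**The case against.** The strongest case against the point has four parts.

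First, with one session, the literal end of treatment is the day of the session, when nothing can yet have worsened or recurred. The phrase must then be loose wording for the end of the study, the time that the recurrence outcome already fixes. This largely stands, and it is why end of study is taken here as the likelier intent. It is not conclusive: section 3 gives the end of treatments a calendar date at which early participants have months of follow-up behind them. The recurrence outcome sets a time for recurring lesions only, so nothing elsewhere corrects the time for worsening ones.

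Second, a reader might infer that staff must either break the blind or leave the rule unused. The protocol does not support that. Section 3.6 provides an investigator who properly knows every allocation, and section 3.10 does not say who decides on cryotherapy. What remains is the information carried by the offer itself. The separation of roles is also less clear than section 3.6 suggests, because section 3 has the principal investigator, who collects the outcomes, giving the dermatological treatment.

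Third, once a participant's 12-month count is done, learning the arm cannot change that count, and with all treatments finished by October 2024 it cannot change allocation. This stands for end-of-study timing.

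Fourth, the wording is permissive and does not forbid cryotherapy in G1. G1 is covered for recurrence and for suspected malignancy, and the protocol calls worsening unlikely. This narrows the gap to worsened, non-recurring, non-malignant lesions in G1, probably few. It does not remove the difference between arms in what is offered.

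**Conclusion.** The point holds in a limited form. The protocol states a trigger that differs by arm. The blinded assessor cannot apply it, and if the treating investigator does, the offer or its absence tells the assessor and participant something about whether the participant is in G1. This is true under either timing, as is the unequal offer of care. The shift from 25% to 0%, or to between 25% and 100%, concerns only participants whose lesions worsen, and it rests on equal worsening rates and an assumed freezing fraction.

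The two stated times also disagree. A reader might go further and infer that the primary outcome is biased in favour of the experimental arms. The documents do not support that as it stands: the bias is nil under end-of-study timing, the likelier intent, and arises only if lesions are frozen before the 12-month count.

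This is a fault in a stated care rule that sits badly with the blinding section, not a detail left for a statistical analysis plan. It should be corrected, and the correction is small.

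**What to change.** Replace the sentence in section 3.10 with one rule: cryotherapy of non-malignant lesions, whether worsening or recurring, has the same trigger in all four arms, is decided without knowledge of arm, and takes place after the participant's 12-month count. Keep the immediate treatment of suspected malignancy as it is.

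If end of study was already meant, the timing part is only a change of wording. Including G1 adds a few cryotherapy procedures. If earlier cryotherapy was intended, the change affects care, because participants with worsening non-malignant lesions would wait until month 12.

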**São Paulo, SP**

**2024**

**Abstract**

The multifocality of actinic keratosis, the unpredictability of lesion progression with possible development into squamous cell carcinomas (SCC), and the consequent risk of local extension and metastasis, along with the recent development of new therapies, make selecting the appropriate therapeutic regimen a challenge. The increasing incidence, associated economic costs, and impact on quality of life have fueled interest in studying treatment protocols for this serious skin condition. The topical application of 16% methyl aminolevulinate (MAL) is well-established in the literature due to its local therapeutic effects and ease of application. However, the high cost of the medication, long incubation time, and adverse effects such as itching and burning experienced by some patients limit the widespread use of this treatment. Studies testing alternative protocols for this promising therapy are needed to increase acceptance among patients and professionals. Therefore, the objective of this protocol is to compare the efficacy of topical application of methyl aminolevulinate (MAL) in concentrations of 8% and 16%, mediated by red light, and to evaluate the impact of different incubation times (1 or 3 hours) in the treatment of actinic keratoses on the face, with a 12-month follow-up. This randomized controlled clinical trial with parallel arms and a 12-month follow-up will consist of 4 groups: G1 - Control Group - MAL 16%, irradiated with 643nm light at 75 J/cm² and a 3-hour incubation time (n=36); G2 - MAL 16% with a 1-hour incubation time (n=36); G3 - MAL 8% with a 3-hour incubation time (n=36); and G4 - MAL 8% with a 1-hour incubation time (n=36). The researcher collects the data, and the participant will be blinded to the interventions. The primary outcome will be the complete remission of the lesion after 12 months. Secondary outcomes will include treatment success (75% reduction in the initial number of lesions), recurrence rate, development of SCC, incidence of adverse effects, improvement in skin texture, wrinkles, and pigmentation using a validated scale. All outcomes will be evaluated at 30 days, 3, 6, 9, and 12 months. Quality of life will be assessed using the Actinic Keratosis Quality of Life questionnaire (AKQoL) at 6 months, together with the Face-Q. If the data follow a normal distribution, they will be analyzed using a two-way ANOVA and presented as means ± standard deviation (SD). Otherwise, they will be presented as medians and interquartile ranges and compared using the Kruskal-Wallis test. Categorical variables will be assessed using the chi-square, Fisher's exact, or likelihood ratio tests. A p-value of < 0.05 will be considered significant.

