Pain, erythema, and post-treatment inflammation tend to be the most common and significant side effects associated with PDT, although rare events have also been documented (Fargnoli et al., 2018; Arcuri et al., 2023), including anaphylaxis and pustular erosive dermatosis. Of the mentioned side effects, pain, in particular, represents a notable adverse event that has limited the widespread use of this procedure. When compared, ALA is more commonly associated with pain than treatments using MAL as a photosensitizer (Fargnoli et al., 2018; Arcuri et al., 2023).

Four randomized studies have demonstrated the efficacy of MAL-mediated PDT combined with sunlight compared to conventional light in participants with actinic keratosis of the face and scalp (Ruber et al., 2014; Lacour et al., 2015). However, when evaluating efficacy according to the degree of actinic keratosis, it was found that sunlight is less effective for grade II and III lesions, with clinical response in 36% and 25%, respectively, compared to conventional PDT with clinical response in 61% and 46% (Fargolini et al., 2015).

The relationship between sun exposure for 1.5 to 2.5 hours and the efficacy of treatment with MAL-mediated PDT was evaluated by Wiegell et al. (2012), and no statistical difference was found between the groups. This multicenter randomized clinical trial showed different cure rates among the types of treated lesions: 75.9% of grade I actinic keratoses, 61.2% of grade II, and 49.1% of grade III had a complete response after three months. A total fluence of 3.5 J/cm² was considered the minimum effective dose, as no association was found between increased fluence and improved response beyond this dose. Eighty-six percent of grade II and 94% of grade III lesions reduced their severity grade or had a complete response with treatment.

MAL-mediated PDT combined with sunlight for the treatment of mild to moderate actinic keratosis on the face and scalp is effective with the advantage of significantly reducing pain, being described as well-tolerated and nearly painless due to the continuous activation of small amounts of porphyrins (Wiegell et al., 2009; Lacour et al., 2015; Fernández-Guarino et al., 2022).

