The multifocality of actinic keratosis, the unpredictability of lesion evolution with potential progression to SCC, and the consequent risk of local extension and metastasis, combined with the recent development of new therapies, make selecting a treatment regimen challenging. Additionally, the increasing incidence of the condition and its associated economic costs and impact on quality of life have fuelled interest in revising treatment protocols for this serious skin condition. The topical application of 16% methyl aminolevulinate is well-established in the literature for its local therapeutic effects and ease of application. However, the high cost of the medication, long incubation time, and adverse effects such as itching and burning are factors that limit the widespread adoption of this treatment. Studies testing alternative protocols for this promising therapy are needed to increase its acceptance among patients and healthcare professionals. Lower concentrations could make the product more affordable and reduce adverse effects (Braathen et al., 2008), though further studies are necessary to increase the level of evidence. Additionally, the three-hour incubation period discourages professionals and patients from choosing this therapeutic option for treating the condition.

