**2.2. Specific Objectives**

**•** To evaluate complete remission (100% remission) of the lesions in relation to the initial number of facial lesions at 3 months (primary objective);

• To evaluate complete remission (100% remission) of the lesions in relation to the initial number of facial lesions at other time points: 30 days, 9 months, and 12 months;

• To evaluate treatment success (75% reduction in the initial number of lesions in the treatment area compared to baseline) at 30 days, 3, 6, and 12 months;

• To evaluate the recurrence rate (reappearance of lesions in previously treated areas) at 30 days, 3, 6, and 12 months;

• To prevent squamous cell carcinoma (conduct assessments to verify the occurrence of squamous cell carcinoma. Cases will be recorded and treated as necessary. Evaluations will be carried out at 30 days, 3, 6, and 12 months);

• To evaluate the incidence of adverse effects through participants’ self-completed diaries and researcher notes. Assessments will be conducted at 30 days, 3, 6, and 12 months;

• To assess postoperative pain, if it occurs, after treatments using the visual analog scale (VAS) at 0 days, 30 days, 3, 6, and 12 months;

• To evaluate the amount of analgesics consumed weekly during the first week after treatment;

• To assess improvements in skin texture, wrinkles, and pigmentation using the scale by Tina Alster et al. (2005) at 30 days, 3, 6, and 12 months;

• To assess participants' quality of life using the Actinic Keratosis Quality of Life questionnaire (AKQoL) (Vilhena et al., 2022) after 6 months of treatment;

• To assess participants' quality of life using the Face-Q questionnaire (Klassen et al., 2015) after 6 months of treatment.

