**3.9.1. Treatment with Topical MAL Photosensitizer**

Before the treatment, the treated area will be cleansed with 0.2% aqueous chlorhexidine. Following this, a light curettage will be performed on the facial area using a sterile curette.

After curettage, a thin layer of the photosensitizer, approximately 1 mm thick, will be applied to the affected areas of the participant's face. An occlusive dressing will then be applied to enhance the penetration of 8% or 16% MAL. This dressing will be covered with aluminum foil to protect from light, preventing ambient light from influencing the protoporphyrin production process.

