• **Incidence of adverse effects -** The incidence of adverse effects, such as erythema, edema, itching, and peeling, will be monitored through a personal diary kept by the participant, in which detailed descriptions of any adverse effects will be recorded. As Jansen et al. (2019) recommended, this method will allow participants to report their symptoms individually. The principal investigator, a dermatologist specializing in this type of treatment, will offer continuous assistance and follow-up, remaining accessible as needed.

• **Subjective pain assessment** - Subjective pain will be assessed using the Visual Analog Scale (VAS), consisting of a 10-mm line with closed ends, indicating "0" for no pain and "10" for unbearable pain, the worst pain ever felt. The same operator will consistently provide instructions for marking the scale. Each participant will be instructed to mark with a vertical line the point that best reflects the intensity of their pain at the time of assessment, following the guidelines of Bottega et al. (2010). These assessments will be conducted weekly for up to 30 days after treatment, followed by evaluations at 3, 6, and 12 months.

[figure not shown]

Figure X: VAS - Visual Analog Scale for Pain. Source: the author

**Rescue Medication**: Rescue medication will be assessed by the standardized amount of analgesics consumed (paracetamol). At the start of the study, each participant will receive a blister pack of paracetamol®, a drug with purely analgesic effects, as Jóźwiak-Bebenista (2014) recommended. Participants are instructed to keep the blister pack until the end of the experiment and bring it to each appointment. At the end of the study, the number of tablets used will be evaluated in each group as a pain measurement parameter. In cases of reported allergy during anamnesis, dipyrone or ibuprofen may be prescribed as alternatives (WAHBA, 2004; TOMS, 2010).

• **Evaluation of Skin Texture, Wrinkles, and Pigmentation**: This evaluation will be conducted at 30 days, 3, 6, and 12 months, using the scale by Tina Alster et al. (2005). This scale, assessed by professionals and participants, classifies improvements as minimal (<25%), moderate (25%-50%), significant (51%-75%), and excellent (>75%). These evaluations will provide a comprehensive approach to measuring the effectiveness of the treatment over time.

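### Erythema, edema, itching and peeling are compared only as incidence, with no severity grade, so a regimen that makes these reactions milder could go unrecognised

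*Protocol*

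**What the plan says.** Protocol section 3.10 makes adverse effects a secondary outcome: "The incidence of adverse effects, such as erythema, edema, itching, and peeling, will be monitored through a personal diary kept by the participant". It describes the diary as one "in which detailed descriptions of any adverse effects will be recorded". Section 2.2 sets the matching objective as incidence, from "self-completed diaries and researcher notes. Assessments will be conducted at 30 days, 3, 6, and 12 months". Neither section gives a grade, a duration or a threshold for these reactions.

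The Results Analysis section sends categorical variables to the chi-square, Fisher's exact or likelihood ratio test, and non-normal quantitative variables to Kruskal-Wallis.

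Section 3.10 does set scales for other outcomes: a visual analog scale for pain, a tablet count for analgesic use, and a four-level improvement scale for skin texture, wrinkles and pigmentation.

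On the reasons for the trial, the Justification says: "Lower concentrations could make the product more affordable and reduce adverse effects". It also calls for protocols that mitigate adverse events. The Contextualization cites a review that proposes shorter incubation as a way to limit pain and inflammation.

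**The concern.** All four arms receive the same preparation ("a light curettage will be performed on the facial area using a sterile curette"), then MAL under occlusion and the same 75 J/cm². The Contextualization says: "Pain, erythema, and post-treatment inflammation tend to be the most common and significant side effects associated with PDT". If erythema occurs in most participants of every arm, a better-tolerated regimen would show mainly as milder erythema. A yes/no record counts a mild and a severe reaction alike.

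This is a data-collection choice, which the protocol fixes. An analysis plan can choose a test, but it cannot supply a grade that was never recorded. The first scheduled researcher assessment is at 30 days, so the acute reaction depends on the diary. At stake is whether the trial can show that 8% MAL or 1-hour incubation gives milder skin reactions.

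**Working it through.** **The plan's own figure.** Section 3.1 gives 36 per group from 64% v 91% complete response, 80% power and a chi-square test. The formula used is the normal approximation with pooled variance under the null:

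power = Φ{ [d√n − 1.96·√(2p̄(1−p̄))] / √(p₁(1−p₁) + p₂(1−p₂)) }, with d = |p₁ − p₂| and p̄ the mean of the two proportions.

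With two-sided α = 0.05 this gives 37 per group for 80% power, and 79.6% power at 36. The stated size is reproduced, but it was set for lesion response, not for adverse effects.

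**Inputs.** From the protocol: 36 per arm; 36 + 36 = 72 per level when arms are pooled by concentration or by incubation time; 5% significance level (two-sided assumed). Assumed, because the documents give no rates: control incidence, a normally distributed underlying severity, and a 0.5 SD fall under the reduced regimen.

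**Step 1: what the shift does to incidence.** Reduced-regimen incidence p₂ = Φ(Φ⁻¹(p₁) − 0.5).

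- p₁ = 80% gives p₂ = 63.4%
- p₁ = 90% gives p₂ = 78.3%
- p₁ = 95% gives p₂ = 87.4%

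The same change in severity moves incidence by 16.6, 11.7 and 7.6 points respectively.

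**Step 2: power on any/none, worked for 95%.** d = 0.076, p̄ = 0.912, √(2p̄(1−p̄)) = 0.401, √(0.0475 + 0.1101) = 0.397.

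- n = 72: (0.076 × 8.485 − 1.96 × 0.401)/0.397 = −0.35, power 36%
- n = 36: (0.076 × 6 − 1.96 × 0.401)/0.397 = −0.83, power 20%

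At 72 v 72 the same formula gives 60% at 80% incidence and 49% at 90%. Simulation gives 61% and about 50%.

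**Step 3: power on a 0–3 grade.** The same underlying severity is cut into none, mild, moderate and severe (5/25/45/25% in the control at 95% incidence) and compared by Mann-Whitney, by simulation.

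| Control incidence | n per side | Chi-square, any/none | Rank test, 0–3 grade |
|---|---|---|---|
| 80% | 72 | about 61% | about 77–79% |
| 90% | 72 | about 50% | about 78–79% |
| 95% | 72 | about 36% | about 77–79% |
| 95% | 36 | about 20% | about 49% |

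Fisher's exact test, which the protocol also allows, is lower still at 95% incidence: about 27% at 72 v 72 and 8% at 36 v 36.

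**Step 4: does the gain need a ceiling?** At 50% control incidence and 72 v 72, chi-square has about 65% and the grade about 71%. The grade still does slightly better; the gap widens as incidence rises.

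**The case against.** The strongest case against has four parts.

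- **The ceiling is not documented.** A reader might infer that all four reactions occur in nearly everyone, so that incidence must sit at its maximum. The protocol does not support that. It calls erythema and inflammation among the most common side effects, which is not the same as near-universal. For itching it points the other way: "adverse effects such as itching and burning experienced by some patients limit the widespread use of this treatment". Edema and peeling have no stated frequency. This stands, and the loss of power is therefore conditional on the rate.
- **Tolerability is measured elsewhere.** A reader might infer that the tolerability question goes unanswered. It does not: pain has a visual analog scale from the day of treatment, and analgesic use is counted. The Contextualization singles out pain as the adverse event that has limited use of the procedure. This stands; the gap is confined to the skin reactions. Adverse effects are also only one of the stated reasons for the trial, beside cost and incubation time.
- **Descriptions could be graded afterwards.** A blinded assessor could code the diary entries. This stands in part. With no stated scale, the result would depend on how much each participant wrote and would not be reliably comparable between participants.
- **Sample size also limits.** At 36 per arm even the grade reaches only about 49% for this shift, and at moderate incidence sample size is the main constraint. This stands, but it is no reason to keep the less informative measure.

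Incidence is also a legitimate safety outcome that readers need, so it should be kept.

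**Conclusion.** The point holds in a limited form. The protocol compares erythema, edema, itching and peeling only as incidence, from a diary with no severity scale, while giving reduced adverse effects as one reason for the lower concentration and shorter incubation. For these reactions an any/none comparison is less able than a grade to show a milder course. Under the assumed 0.5 SD shift at 72 v 72, the difference is about 16–18 percentage points of power at 80% incidence and about 40 at 95%.

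These sizes rest on assumed rates, an assumed shift, a normal severity model and one reaction tested at a time. They do not show that the comparison will probably find no difference: at 80–90% incidence, detection is about as likely as not or better. The case for a grade does not depend on proving a ceiling, since the grade did at least as well at every incidence tried. It is a worthwhile improvement to a secondary outcome and does not threaten the main result.

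**What to change.** Print a 0–3 grade (none, mild, moderate, severe) for each of erythema, edema, itching and peeling in the planned diary, for the acute period after treatment. In section 3.10, name the worst grade per reaction as the compared value, using a rank or ordinal test. Continue to report incidence, defined as grade 1 or more, for all reactions; it follows directly from the grade, so nothing is lost. Align the objective in section 2.2 with this wording.

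The cost is one structured diary page, a sentence or two of protocol text, and slightly more for participants to fill in. It helps only participants whose acute period is still to come, because a grade not recorded at the time cannot be reliably recovered.
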